### Pharmacological Treatment for Cognitive Problems

Cholinesterase inhibitors (ChEI), although modest in effect, are the most useful pharmacological treatment available for Alzheimer's Disease and vascular dementia [2,34]. Although not curative, their effects include memory stabilization and delays in functional decline and nursing home placement [2].

The molecular mechanism of action of ChEI is through increased cortical and hippocampal acetylcholine, an important neurotransmitter for memory regulation and neural plasticity. However, the mechanism of the clinical improvements in delaying functional decline is not well understood. One possible explanation may relate to not only the cognitive action of the drug, but also to subtle improvements in the motor function of these patients. Whether by direct effect or mediated through cognition, motor function improvement would consequently serve to stabilize mobility and delay functional decline. In Figure 1, we propose possible levels of action of ChEI on motor function and gait.

**Figure 1 F1:**
[figure not shown]
**Regulation and Neural Control of Gait**.

Cholinesterase inhibitors have also been tried in individuals with MCI, with the goal of delaying the progression to dementia. A recent RCT demonstrated that cognitive enhancers might improve cognition in this population; however, the effect was weak and had questionable clinical significance [12]. Currently, there is no indication to use cognitive enhancers to treat people with MCI with the goal of delaying or preventing further functional or mobility decline.

Recently, it has been suggested that ChEI may improve gait performance [35] through an improvement in attentional resource allocation due to the fact that ChEI are known to improve attention and executive function [34]. Besides this effect on mobility through cognition, cholinergic neurotransmission has a potential effect on mobility and gait regulation not mediated through cognitive improvement since cholinergic neurons in the striatum are involved in movement and motor functions. For instance, dysfunction of cholinergic neurons in the striatum is known to occur in movement disorders (such as Huntington's chorea), and an imbalance between dopaminergic and cholinergic transmission is found in Parkinson's disease and related drug-induced dyskinesias [36]. These related findings lend both clinical and mechanistic plausibility to the hypothesis that cognitive enhancers may also have a potential effect on motor function and gait.

### Effect of cognitive enhancers on motor function

Despite the well-recognized effect of cognitive enhancers on cognitive status, there is a shortage of studies investigating their effect on motor functioning, especially on walking, which will most likely have an impact on fall risk in this population. A recent pilot study has shown that fine motor skills as evaluated by hand movements improved with cognitive enhancer treatment [37]. This was an open label study in 12 patients with Alzheimer's Disease (AD) using the ChEI, donepezil, at 5 mg/day for 4 weeks then increased to 10 mg/day for 8 weeks. The investigators noted a trend toward improved (i.e. faster) finger tapping scores following donepezil treatment. Similarly, a case series showed that individuals with dementia taking galantamine (a cholinesterase inhibitor similar to donepezil) for 24 weeks had less decline in gait performance compared with age matched controls [35]. Nevertheless, there have been no studies to date evaluating the effect of ChEI on fall risk, balance confidence, and gait variability in elderly people with Mild Cognitive Impairment.

### Pilot data and Rationale

As a proof of principle for this proposed RCT, we assessed the effect of donepezil, over four months of treatment, on gait using an electronic walkway (GAITRite System) in six individuals with AD [38]. An increase in gait velocity and a reduction in gait variability were seen following cognitive enhancer treatment. In brief, participants with AD taking donepezil increased their mean gait velocity (G-vel) after one month (from 89.7 ± 11 to 106.9 ± 22, *p *= .045) under a single-tasking condition. These increases were sustained and improved after four months, suggesting a dose-response pattern as shown in Figure 2. Gait variability (G-var), assessed as coefficient of variation of stride time, decreased during follow-up (single-task from 22.3 to 11.30, *p *= .04). Since it is known that gait performance declines over time in older people, we compared these results with observational data from eight comparison individuals with MCI and found that the MCI group experienced a reduction of gait velocity over time. (Figure 2)

**Figure 2 F2:**
[figure not shown]
**Changes in Gait Velocity in people with early Alzheimer's disease (AD) taking donepezil (intervention group) and Mild Cognitive Impairment (MCI; control group)**.

Although the small sample size and the lack of randomization are limitations of this open label study, these preliminary findings provide preliminary data and rationale for pursuing the current clinical trial. We will assess whether donepezil treatment will improve gait performance under single and dual-task conditions in older individuals with MCI by comparing them with MCI controls receiving placebo. Additionally, we will test the effect of the intervention on two well-established clinical markers of fall risk such as balance sway and the balance confidence scale (ABC) [39], and also on the actual number of falls. All assessments will be completed over a 6-month follow-up period.

Currently, there is no clinical indication for prescribing cognitive enhancers in people with MCI, so there is genuine equipoise about the effect of cognitive enhancers on gait, balance, and risk of falls in this population.

## Methods/Design

### Design

Double blinded randomized controlled trial with 6 months follow-up in 140 older individuals with MCI. Participants will be randomized, in blocks of four, to the control and the intervention groups (Figure 3).

**Figure 3 F3:**
[figure not shown]
**Trial Design**. Adapted from the CONSORT diagram [61,62].

### Participant Selection

Our pilot study referenced above has given us preliminary research experience with this patient population. Participants will be recruited from the Aging Brain and Memory Clinic at Parkwood Hospital. The clinical investigators will enrol an average of five (5) participants per week, thereby recruiting the 140 participants over a period of 7 months. In order to maximize enrolment possibilities, the recruitment period will be extended to 10 months if the 140 participants are not reached at month 7.

#### Inclusion criteria

• patients who have MCI (diagnosed using criteria suggested by Winblad et al [13])

• Aged 65 years and older

• Able to walk independently 10 meters without any gait aid (for example: walker, cane)

• Able to travel to the clinic for the assessments

#### Exclusion criteria

• Unable to understand English

• History of psychiatric illness within the last two years, including depression

• Parkinsonism or any neurological disorder with residual motor deficit (e.g. stroke, epilepsy)

• Musculoskeletal disorder detected by clinical examination which affects gait performance

• Active osteoarthritis affecting the lower limbs (America College of Rheumatology criteria [40-42])

• Chronic Bradycardia (baseline heart rate below 60 beats/minute)

• Use of psychotropic medication, which can affect motor performance (e.g. neuroleptics and benzodiazepines)

• Depression (score above 8/15 on the Geriatric Depression Scale – GDS [43,44]) since depression has been shown to reduce gait performance.

In order to increase generalizability of the results, the inclusion/exclusion criteria have been restricted to factors that can compromise study adherence and gait evaluation. The exclusions are to reduce the statistical noise introduced by specific diseases or disabilities that have strong known effects on gait. Exclusions will be based on a formal medical examination. The diagnosis of MCI is based on clinical criteria [15,45], which includes the presence of subjective memory complaints from the patient and family, objective memory impairment, preserved general intellectual function assessed clinically, absence of significant functional impairment, and absence of clinical dementia as assessed by a skilled geriatrician with extensive experience in a memory clinic setting. Objective memory impairment is operationalized, following the criteria set out by Petersen and colleagues [11]; demonstrated by memory impairment judged as beyond the normal range for age and education by a skilled geriatrician. Additionally, global cognition will be assessed using the Mini Mental State Examination (MMSE; scored 0–30), and the Montreal Cognitive Assessment (MoCA; scored 0–30, with higher scores indicating better performance). The MoCA test is a validated tool used to assess global cognition and was originally created to assist in the diagnosis of MCI [46]. In brief, when considering MMSE and MoCA performance in the same individual, a pattern of low MoCA score (<26) with normal MMSE score (>26) is associated with the diagnosis of MCI [46].

The Health Sciences Research Ethics Board at The University of Western Ontario approved the research protocol – Research Protocol Number 16086. This RCT has been registered in clinical trials.gov (identifier number: NCT00934531)

### Measurements and Procedures

All participants will undergo a baseline, one month, and a final six-month assessment. Baseline gait assessment will occur within one week prior to starting donepezil (T0), with a second assessment occurring after 4 weeks of treatment at 5 mg of medication (T1). The third and final assessment will occur after participants have been on the full dose of donepezil, 10 mg, for a period of 5 months (T2), yielding a total period of follow-up of 6 months from baseline. Assessments at each of these time-points will include gait analysis, balance sway, and balance confidence as well as cognitive measurement of attention and executive function. Falls will be retrieved by phone interview as has been done in previous studies [47,48]. A timeline for the proposed study can be found in Figure 4.

**Figure 4 F4:**
[figure not shown]
**Schematic timeline of the proposed RCT**.

#### Hypothesis and Objectives

• **Hypothesis 1: **Cognitive enhancers reduce fall risk in elderly people with MCI by improving their gait performance.

• **Hypothesis 2: **Cognitive enhancers improve balance and balance confidence in elderly people with MCI.

• **Mechanistic Hypothesis: **The improvement on gait and balance measures is due to an enhancement in attention and executive function.

• **Objective 1: **To assess the effect of donepezil on gait velocity and gait variability in elderly people with MCI using an electronic walkway (Gait Rite System, CIR Systems Inc.).

• **Objective 2: **To evaluate the effect of donepezil on balance and in balance confidence in elderly people with MCI using a balance platform (Bertec Inc.) and the Activities-Specific Balance Confidence Scale (ABC).

• **Objective 3: **To test if these potential improvements on gait and balance are mediated through an enhancement in attention and executive function.

### Outcomes measures

#### Primary outcomes

1. Improvements in gait velocity (cm/second) at month six

2. Reduction in gait variability assessed as standard deviation (SD) and coefficient of variation (CoV) at month 6.

#### Secondary outcomes

Between-group improvement in:

1. Balance confidence as evaluated by the Activities-Specific Balance Confidence Scale (ABC)

2. Balance sway, maximum saggital displacement, using a force platform (Bertec Inc.)

3. Attention measured with the Digit Span Test

4. Executive function using the Trail Making Test, parts A and B

5. Reduction of number of falls: The total number of falls by month 6 (T2) and proportion of participants who fall are also secondary outcome measures to be evaluated.

### Randomisation

Once informed consent has been obtained and the baseline assessment has been completed, participants will be allocated to one of the two arms at a ratio of 1:1. Stratified randomization within strata based on fall history (0 falls, 1+ fall in past 12 months) will be performed. A block randomization by four will be applied to ensure a cumulative balance of participants between arms. The randomization sequence of the participants will be generated by a computer program and allocation to groups will be done with sequentially numbered opaque sealed envelopes. A professional bio-statistician not involved in recruitment and assessment will perform the randomization

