### Tolerance to the medication

Donepezil is judged to be fairly well tolerated in older people at the 10 mg/day standard dose regimen. We selected Donepezil for our study since, according to the last Cochrane Review on cholinesterase inhibitors [59], fewer patients suffer adverse events on Donepezil when compared with other cognitive enhancers such as Rivastigmine. The most common reported intolerance is due to gastrointestinal problems such as abdominal pain, anorexia, nausea, vomiting, diarrhoea, and rarely dizziness, headache, and insomnia, which were significantly more frequent in the ChEI than in placebo groups in the referenced meta-analysis. Participants who would develop gastrointestinal intolerance with Donepezil at 10 mg/day will have the dose reduced to 5 mg/day and switched to a bedtime regimen as per current clinical practice. Participants who have persistent intolerance, and anyone who experiences a major adverse reaction, will be withdrawn from the study and the events reported to the Research Ethics Board and to Health Canada.

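### One fixed, published block size of four at a single clinic avoidably weakens allocation concealment and, after a code break, the blind of others in the same block

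*Protocol article*

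**What the plan says.** The block size appears in the Abstract, in Design ("Participants will be randomized, in blocks of four, to the control and the intervention groups") and in Randomisation ("A block randomization by four will be applied to ensure a cumulative balance of participants between arms"). No other size is mentioned.

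Randomisation also sets the ratio ("participants will be allocated to one of the two arms at a ratio of 1:1") and the strata ("Stratified randomization within strata based on fall history (0 falls, 1+ fall in past 12 months) will be performed"). It names two safeguards: "allocation to groups will be done with sequentially numbered opaque sealed envelopes", and "A professional bio-statistician not involved in recruitment and assessment will perform the randomization". The sequence is computer-generated.

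Participant Selection gives one source of participants ("Participants will be recruited from the Aging Brain and Memory Clinic at Parkwood Hospital"), a pace of five per week, and 140 participants in 7 months, extendable to 10 months. The comparator is placebo and the trial is called double blind.

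Tolerance to the medication lists gastrointestinal complaints and, rarely, dizziness, headache and insomnia, "which were significantly more frequent in the ChEI than in placebo groups in the referenced meta-analysis". The same section calls donepezil fairly well tolerated.

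**The concern.** Permuted blocks protect concealment only while staff cannot tell where a block starts and ends. Here the size is constant and public, and the stratum is a fact known at enrolment. One clinic sees the whole sequence, so block membership can be reconstructed from the enrolment log. Any knowledge of earlier arms then carries over to others in the block, by two routes.

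- **Selection.** A predictable next allocation could influence whom the investigator enrols. Eligibility rests partly on clinical judgement (Exclusion criteria; Evaluations).
- **Blind.** If one participant's code is broken, the odds change for three other identifiable participants, who may be under assessment up to month 6. Staff with a view on the arm could affect outcomes that pass through people. Balance confidence is self-rated, questionnaires are completed under staff supervision (Follow-up), and late or incomplete fall calendars are completed by phone with the research assistant (Falls).

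**Working it through.** The article states no predictability figure, so there is none to reproduce. Inputs from the article: block size 4, ratio 1:1, two strata, five enrolments per week, first on-treatment assessment at 4 weeks. Side-effect rates, stratum shares and delays are assumptions, shown as ranges.

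**1. Worst case: every earlier arm in the block is known at once.** There are 6 equally likely blocks of two and two.

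| Place in block | Certain | Best guess correct |
|---|---|---|
| 1 | 0 | 1/2 |
| 2 | 0 | 2/3 |
| 3 | 1/3 (first two match) | 1/3 × 1 + 2/3 × 1/2 = 2/3 |
| 4 | 1 | 1 |

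Certain: (1/3 + 1)/4 = 33.3%. Correct: (1/2 + 2/3 + 2/3 + 1)/4 = 2.833/4 = 70.8%.

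**2. Arms inferred only from side effects, seen at once.** For each pattern of side effects among earlier block members, the six blocks are weighted by their likelihood and the likelier arm is guessed for the next participant.

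| Assumed rate, drug / placebo | Next allocation guessed correctly |
|---|---|
| 20% / 10% | 52.0% |
| 40% / 20% | 53.2% |
| 40% / 10% | 55.1% |
| 60% / 10% | 58.4% |
| 80% / 5% | 63.9% |

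**3. Timing.** A stratum with share f fills a block in 4/(5f) weeks: 4/(5 × 0.8) = 1.0 week to 4/(5 × 0.2) = 4.0 weeks. The next table comes from simulating 140 arrivals at 5 per week (smaller-stratum share 20% to 50%), with earlier arms fully known only after a delay.

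| Delay | Correct | Certain |
|---|---|---|
| 0.5 week | 58–60% | 10–12% |
| 1 week | about 54% | about 4% |
| 2 weeks | about 51% | about 1% or less |
| 4 weeks | about 50% | about 0% |

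Slower recruitment lengthens this window. At 10 months the pace is 140/(10 × 4.345) = 3.2 per week, and a 20% stratum then needs 4/(3.2 × 0.2) = about 6 weeks per block, which is past the 4-week assessment.

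**4. A participant's own arm.** From that person's side effects alone, the guess is right with probability ½(p_drug + 1 − p_placebo): ½(0.20 + 0.90) = 55% and ½(0.40 + 0.90) = 65%. Adding the side effects of the other block members and the block constraint left the average accuracy unchanged at 55% and 65%.

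**5. After a code break.** One revealed arm leaves three members, two of them in the opposite arm, so each moves from 1/2 to 2/3. Two revealed members of the same arm make the other two certain.

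**6. Effect of varying the size.** The simulation has 72 participants per sequence, every earlier arm known, and a guesser who knows the possible sizes but not their order.

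| Scheme | Certain | Correct |
|---|---|---|
| Fixed 4 | 33% | 71% |
| Random 4/6/8, withheld | about 2% | about 68% |

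Almost all the gain is in removing certainty; average guessing improves by only about 3 points.

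**The case against.** The strongest reply is that prediction needs known arms, and nothing in the article says that arms become known. Placebo masks them. Randomisation provides opaque, sealed, numbered envelopes and a biostatistician outside recruitment and assessment. The side-effect signal is weak and often arrives after the block has closed. All of this stands, and it is why 33% and 71% are upper bounds and not expected values.

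It also stands that guessing an arm from side effects happens with any block size (step 4), so that risk cannot be charged to the blocks. Gait is recorded by an automated walkway after standardised instructions, which limits any effect on the primary outcomes. It does not remove it, because pace is self-selected and staff prompt participants who stop.

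A reader might infer two stronger claims:

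- **The envelopes reveal the arm.** The article does not say what they contain or who opens them. A pack code fits the wording equally well, and such detail is commonly left to the full protocol.
- **Neither concealment nor the double blind is secure.** That would require earlier arms to be disclosed, and the article does not say that they are.

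The reply does not defend the fixed size itself. Publishing it gave up the one element of the scheme that could have been withheld. Block closure ends the selection route but not the code-break route, which stays open throughout follow-up.

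**Conclusion.** The point holds as an avoidable weakness, not as a failure of concealment or blinding. The ceiling is 33% certain and 71% correct guesses, and it applies only if all earlier arms are known. With side effects as the only source, seen at once, correct guesses run from about 52% to 64% over the assumed rates. At the planned pace, information delayed by two weeks or more adds almost nothing.

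The realistic risk is small to moderate. It is greatest for blocks that fill slowly and for participants who share a block with someone whose code is broken. It bears mainly on balance confidence and reported falls. The low cost of the remedy is what justifies acting. The conclusion rests on staff being able to track enrolment order by stratum, and on the assumed rates, shares and delays, since the article gives none.

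**What to change.** Keep 1:1 allocation stratified by fall history. Have the independent biostatistician generate blocks of randomly varying size, for example 4, 6 and 8, and withhold the sizes and their order from all site staff until unblinding. Protocol text available to the site should say only that permuted blocks of varying size are used.

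This removes nearly all certain allocations and leaves staff unsure who shares a block with an unmasked participant. It does not address guessing from a participant's own side effects.

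The cost is one setting in the randomisation program, with ratio, strata and sample size unchanged. The downside is a larger possible end imbalance. An unfinished block of 8 can be off by 4 and a block of 4 by 2, so the maximum rises from 2 to 4 per stratum. That is minor in a trial of 140.

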### Follow-up

As shown in the timeline (Figure 4), participants will be followed for 6 months after their baseline measurements. Improvements in the primary outcomes of interest are expected after 4 months of treatment based on our pilot study and on a previous report of the potential effect of cognitive enhancers on gait and mobility. However, a six-month follow-up will increase the probability of finding a significant reduction of the number of falls and the adverse events because of the intervention. The three assessments will be conducted by trained research assistants and all the questionnaires will be checked for missing data and completed with the participants under their supervision.

### Evaluations

Inclusion/exclusion criteria will be verified through a standardized neurological and musculoskeletal examination by the principal investigator.

#### Instrumentation

Gait performance will be assessed using an electronic walkway system (GAITRite^®^) under single and dual-task conditions. The GAITRite^® ^system includes a portable electronic walkway mat (600 cm in length and 64 cm in width) for the automated measurement of spatiotemporal gait parameters. As participants walk along the mat, imbedded sensors are activated by the pressure of their feet and deactivated when the pressure is released. A computer processes the footsteps, providing data for both spatial and temporal parameters. Gait parameters are recorded using only the footprint of the participants, thereby eliminating the need for external sensors attached to the body or lower limbs that may interfere with gait performance or may confuse an older individual with a cognitive impairment. The mat is located in a well-lit, 10-meter long hallway at the Division of Geriatric Medicine at Parkwood Hospital. Start and end points will be marked on the floor with tape one meter from either end of the mat to avoid recording acceleration and deceleration phases.

